## Participants

We will include individuals aged 18–80 years, of any sex, with a first-ever ischemic or haemorrhagic stroke affecting the middle cerebral artery (MCA) or anterior cerebral artery (ACA). Recruitment will occur within seven days of stroke onset, and individuals reporting a Shoulder Abduction and Finger Extension (SAFE) score of <5(0–4) or knee extensor strength of <3/5 on the Medical Research Council (MRC) strength grade within this period will be included. Only those who are medically stable and able to follow simple commands will be included. The exclusion criteria will be individuals with a history of bilateral clinical strokes; those admitted more than seven days after stroke onset; patients who had undergone surgical interventions such as craniotomy or craniectomy; and individuals with pre-existing neurological or musculoskeletal disorders affecting motor functions.

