Despite its advantages, the application of sEMG in early stroke recovery prediction is still unexplored in clinical practice. Currently, the majority of applications focus on biofeedback or rehabilitative monitoring rather than prognostic modelling. The lack of established procedures, limited awareness among clinicians, and differences in signal interpretation may all contribute to this underutilization. Therefore, a thorough examination of the prognostic potential of sEMG is needed, especially during the acute stage of stroke. To bridge this gap, we aimed to develop a prediction model for people with severe motor impairment after stroke, employing surface electromyography to analyse whether the amplitude of muscle activity recorded from upper limb muscles such as anterior deltoid, middle deltoid, long head of biceps brachii, long head of triceps brachii and extensor carpi radialis and lower limb muscles such as tibialis anterior, medial head of gastrocnemius, rectus femoris, and biceps femoris within the first week of stroke could predict upper and lower extremity motor recovery and activity capacity of the upper extremity, postural balance, and walking at 3 months post stroke. These muscles were selected because they represent key proximal and distal muscle groups commonly involved in upper and lower extremity functions, balance and walking functions after stroke [24,25]. We hypothesized that greater sEMG amplitude recorded within the first week post-stroke, reflecting detectable voluntary muscle activity in the absence of visible movement, would be positively associated with upper and lower extremity motor recovery, upper extremity activity capacity, postural balance, and walking ability at 3 months post-stroke.

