## Description of protocol

This is a prospective, single-center cohort study designed for the development and internal validation of a multivariable prognostic model, reported in accordance with the Transparent Reporting of a multivariable prediction model for Individual Prognosis or Diagnosis (TRIPOD) guidelines [26]. This longitudinal single-group cohort study will be conducted at the stroke unit and the neuromotor control unit of a tertiary care hospital in South Karnataka, India. Participants will be selected using a purposive sampling method. This study was approved by the Institutional Ethics Committee (IEC- 123/2025) and registered with the Clinical Trial Registry-India (CTRI/2025/06/088335).

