## Limitations

The study focuses specifically on patients with severe motor impairment during the first 3 months after stroke onset, which limits the generalizability of findings to broader stroke populations. Future studies could apply this protocol to patients with milder impairments, at later post-stroke stages, to improve generalizability and feasibility.

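### Entry on either limb's criterion lets arm and leg results rest partly on limbs that are not severely affected, although the conclusions are framed for severe impairment

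*Protocol article*

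**What the plan says.** Under Participants, the article admits people who, within seven days of onset, have a SAFE score below 5 "or knee extensor strength of <3/5 on the Medical Research Council (MRC) strength grade". The arm and leg criteria are alternatives.

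The Background sets the aim, to "develop a prediction model for people with severe motor impairment after stroke", and asks whether early sEMG "could predict upper and lower extremity motor recovery and activity capacity of the upper extremity, postural balance, and walking at 3 months post stroke". The hypothesis concerns sEMG amplitude "reflecting detectable voluntary muscle activity in the absence of visible movement". Description of protocol gives one cohort without strata: "This longitudinal single-group cohort study will be conducted at the stroke unit". Table 1 schedules arm and leg sEMG and every arm and leg outcome without distinguishing participants by the limb that qualified them. Limitations then describes the sample in the same terms as the aim: "The study focuses specifically on patients with severe motor impairment".

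The baseline grade of a limb has two later roles. SAFE enters an exploratory correlation with sEMG (sEMG analysis), and baseline motor severity is an auxiliary variable for imputation (Missing data). Neither role limits, stratifies or adjusts an outcome analysis by that limb's own criterion.

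**The concern.** Someone with SAFE of 5 or more and a weak knee extensor is eligible and contributes to FMA-UE and ARAT. Someone with SAFE 0–4 and knee extensor strength of 3/5 or more is eligible and contributes to FMA-LE and FAC. In each case one limb entered only because of the other, and it need not fit either the severe-impairment aim or the hypothesis about activity without visible movement.

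The Background justifies the study by saying that clinical prediction is weakest when the deficit is severe. If the analysis mixes limbs on both sides of the cut-off, part of any association may reflect the gap between the two groups and not prediction among severe limbs. Performance in the mixture would then not answer the question the study asks.

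**Working it through.** **The plan's own figure.** Sample size estimation uses n = z²(1 − r²)/d² with z = 1.96, r = 0.6 and d = 0.20. This gives 3.8416 × 0.64 / 0.04 = 61.47, stated as 61. Allowing 20% dropout, 61/0.8 = 76.25, stated as 76. Both reproduce.

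**Effect of mixing.** Let f be the share whose modelled limb does not meet its own criterion, r_w the correlation within each group (taken as equal), and dx and dy that share's shifts in sEMG and outcome in within-group SDs. With k = f(1 − f),

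pooled r = (r_w + k·dx·dy) / √[(1 + k·dx²)(1 + k·dy²)].

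The documents give none of f, dx, dy or r_w, so all four are assumptions. For r_w = 0.2 and f = 20%, k = 0.16:

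| sEMG shift | Outcome shift | Numerator | Denominator | Pooled r |
|---|---|---|---|---|
| +1.5 | −0.5 | 0.20 − 0.12 = 0.08 | √(1.36 × 1.04) = 1.189 | 0.07 |
| 0 | +1.5 | 0.20 | √(1 × 1.36) = 1.166 | 0.17 |
| +0.3 | +1.5 | 0.20 + 0.072 = 0.272 | √(1.0144 × 1.36) = 1.175 | 0.23 |
| +1.5 | +1.5 | 0.20 + 0.36 = 0.56 | 1.36 | 0.41 |
| +2 | +2 | 0.20 + 0.64 = 0.84 | 1.64 | 0.51 |

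The first row represents a change score on which less affected limbs have less room to gain. The next two represent a level outcome when normalisation removes all or most of the sEMG difference. The last two represent a level outcome with a large sEMG difference.

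Varying the share to 10% (k = 0.09) or 30% (k = 0.21), with r_w still 0.2:
- sEMG +1.5, outcome −0.5: 0.1325/1.109 = 0.12, or 0.0425/1.245 = 0.03.
- sEMG +0.3, outcome +1.5: 0.2405/1.101 = 0.22, or 0.2945/1.225 = 0.24.
- Both +1.5: 0.4025/1.2025 = 0.33, or 0.6725/1.4725 = 0.46.
- Both +2: 0.56/1.36 = 0.41, or 1.04/1.84 = 0.57.

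**Precision in a limb's own subset.** With m = 61(1 − f) evaluable, the plan's formula gives half-width = 1.96 × √(0.64/m) at r = 0.6:

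| Share outside the subset | Evaluable m | Half-width |
|---|---|---|
| 0% | 61 | 0.20 |
| 10% | 55 | 0.21 |
| 20% | 49 | 0.22 |
| 30% | 43 | 0.24 |

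**The case against.** A reader might infer that the entry rule fills an arm model with mildly affected arms and so inflates the reported prediction. The documents do not support that, for four reasons.

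- **Endpoint.** Internal validation and model performance says the primary endpoint will be analysed as ΔFMA, whereas Dependent variables (outcome) names the 3-month FMA score. For a change score the distortion can vanish or reverse.
- **Predictor scale.** Procedure divides mean RMS by maximum RMS. If the maximum is the participant's own, this can shrink the sEMG difference between more and less affected limbs.
- **Share.** No expected share of participants with only one limb below its cut-off is given. If it is small, the effect is small.
- **Wording.** A limb not below the cut-off may still be moderately weak, and the article speaks of a prediction model without describing separate arm and leg models.

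It can also be said that a person with one severely affected limb is fairly described as having severe motor impairment, and that analysis sets often sit in a fuller document.

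The first four points stand, and they remove any claim of certain inflation. The person-level reading is fair as a description of the sample, but the outcomes and the hypothesis concern particular limbs. The fuller-document point carries some weight, though the entry rule, the single cohort and the severe-impairment framing are all fixed in this article, and its modelling sections do not connect them.

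**Conclusion.** The point holds as one of applicability. As written, performance for an arm or leg outcome can rest partly on limbs that do not meet that limb's own severity criterion, while the conclusion is framed for severe impairment. For 3-month FMA, ARAT and FAC levels, the association is likely overstated if those limbs are also higher on normalised sEMG. For ΔFMA it may be unchanged or understated.

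The size cannot be fixed from the documents. The 0.07 to 0.51 range around a within-group 0.2 rests on the assumed 20% share, equal within-group correlations and the listed shifts; it shows what is possible and is not a forecast. Because the same remedy serves in either direction and is cheap, it should be adopted. The point does not undermine the study design.

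**What to change.** Prespecify that performance for arm outcomes (FMA-UE, ARAT) is reported in participants with SAFE below 5, and for leg outcomes (such as FMA-LE and FAC) in those with knee extensor strength below 3/5. Base the severe-impairment conclusion on those subsets. The whole cohort may still be used for fitting, with the limb's baseline grade as a covariate; the optimism correction should then be computed for performance in the subset. Record both grades for every participant, since one alone is enough for entry. State how many participants fall outside each subset.

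No entry threshold changes and no extra visit is needed. The cost is the loss of precision tabulated above. Keeping 61 evaluable per limb would instead mean enrolling 76.25/(1 − f), which is about 85, 96 or 109 at shares of 10%, 20% or 30%. That is optional; reporting the wider intervals is enough.

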## Sample size estimation

The sample size was estimated using the following formula:$$n={\left(Z\alpha /2\right)}^{2}\left(1-r^{2}\right)/d^{2}$$where Zα/2 (Confidence Interval) = 95%, CI = 1.96, r (Estimated Correlation value) = 0.6, and d (Precision) = 20%.

Considering the above values, *n* = 61

Thus, with a dropout rate of 20%. *n* = 76

Hence, the final sample size of this prospective cohort study was 76 participants with stroke.

The sample size determination is guided by a widely accepted rule of thumb for prediction modelling, which recommends approximately 10 outcome events per predictor parameter [27]. Based on this principle, the available sample size is expected to support the inclusion of a small and clinically meaningful set of predictors, anticipated to be around 7 (≈7 degrees of freedom) while minimizing the risk of overfitting. Consistent with guidance by Riley et al [28] we considered a target global shrinkage factor of ≥0.90 to limit overfitting and aimed for an anticipated discrimination performance (AUC) of approximately 0.75–0.80. Furthermore, the modelling strategy will incorporate penalised regression techniques and bootstrap-based internal validation to obtain optimism-corrected estimates of discrimination and calibration, consistent with TRIPOD recommendations.

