### Measurement time points

Independent variables (predictors) will be measured at two points: within 7 days of the first-ever stroke onset and at 1st month post-stroke. Dependent variables (outcomes) will also be assessed at two points, at the 1st and 3rd months post-stroke. (Table 1)

**Table 1 tbl0001:** Time points of predictor and Outcome measure assessment.

Measures		Within 7th day	1st Month	3rd Month
**Independent Variable** (Predictor)	sEMG recording of Upper limb muscles	**✔**	**✔**	
	sEMG recording of lower limb muscles	**✔**	**✔**	
**Dependent Variable** (Outcomes)	FMA-UE		**✔**	**✔**
	ARAT		**✔**	**✔**
	FMA-LE		**✔**	**✔**
	FAC		**✔**	**✔**
	10mWT		**✔**	**✔**
	Mini-BEST		**✔**	**✔**
	SIS		**✔**	**✔**

**Abbreviation:** FMA-UE, Fugl Meyer Assessment-Upper Extremity; ARAT, Action Research Arm Test; FMA-LE, Fugl Meyer Assessment-Lower Extremity; FAC, Functional Ambulation Category; 10mWT, 10-meter Walk Test; SIS, Stroke Impact Scale.

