## Statistical methods and analysis

The data will be analysed using R Studio. The normality of the distribution will be verified via the “Kolmogorov‒Smirnov test”. If the data are normally distributed, they will be presented as the mean ± SD; if they are not normally distributed, they will be presented as the median and interquartile range. Categorical variables will be presented as frequencies and percentages, or as medians and interquartile ranges. Spearman/Pearson correlation coefficients will be applied to all predictors and outcomes. Candidate predictors will be specified by using Penalised regression methods (elastic net) for model development to achieve coefficient shrinkage and reduce overfitting.

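### The sample-size section's figures (76 participants, about 7 parameters at 10 events each, shrinkage ≥0.90, AUC 0.75–0.80) are not compatible; the gap is large for the secondary binary models and modest for the continuous primary endpoint

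*Protocol article*

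**What the plan says.** The Sample size estimation section of the protocol article sizes the study on the precision of one correlation, with "r (Estimated Correlation value) = 0.6, and d (Precision) = 20" per cent at 95% confidence. This gives 61, and 76 after 20% dropout: "Hence, the final sample size of this prospective cohort study was 76 participants with stroke".

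The same section then justifies this number for prediction modelling. It cites a rule of "approximately 10 outcome events per predictor parameter", says the sample should support around 7 degrees of freedom, and continues: "we considered a target global shrinkage factor of ≥0.90 to limit overfitting". It also aims for an AUC of about 0.75–0.80. It gives no outcome prevalence, event count, multivariable R² or shrinkage calculation.

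Internal validation and model performance makes the primary endpoint a continuous change in FMA; dichotomous thresholds are secondary. Model development and validation says predictors are prespecified, whereas Statistical methods and analysis says "Candidate predictors will be specified by using Penalised regression methods (elastic net) for model development".

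**The concern.** The study's product is a prediction model, and this section is where a reader learns how well it is protected against overfitting. Event counts and AUC belong to a binary outcome, but the primary endpoint is continuous. The number 7 matches only the enrolled sample divided by 10. Because the shrinkage target stands in the justification for 76, a reader will take it as met with 7 parameters. If it is not, the section overstates what the sample can support, and the analysts have no sound limit on how many candidates to enter.

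**Working it through.** **1. The plan's own figures.** Inputs, all from Sample size estimation: Z = 1.96, r = 0.6, d = 0.20, dropout 20%.

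- n = 1.96² × (1 − 0.36) / 0.04 = 61.47, printed as 61.
- 61 / 0.8 = 76.25, printed as 76. Both reproduce.
- Rounding up instead gives 62, and 62 / 0.8 = 77.5, so 78. The difference is trivial.
- Completers expected from 76: 76 × 0.8 = 60.8, about 61.

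**2. Events rule.**

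- 7 parameters × 10 = 70 events.
- In a binary outcome the rarer class is at most half: 38 of 76, or about 30 of 61.
- At 10 per parameter that supports 3 parameters (38/10 = 3.8; 30/10 = 3.0). With 7 parameters it leaves 38/7 = 5.4 or 30/7 = 4.3 events each, at best.
- Seven follows only from 76/10 = 7.6, with every participant counted as an event and no allowance for dropout. For a continuous endpoint the rule has no meaning.

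**3. Secondary binary models.** Global shrinkage criterion: n = p / [(S − 1) ln(1 − R²cs/S)], with p = 7 and S = 0.90. R²cs (Cox–Snell) is derived from the AUC and prevalence, assuming a normally distributed linear predictor in each outcome class. Prevalence is an assumption, since the protocol gives none.

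| AUC | Prevalence | R²cs | n needed | S at 61 | S at 76 | Parameters at S = 0.90, n = 61 |
|---|---|---|---|---|---|---|
| 0.75 | 20% | 0.126 | 463 | 0.56 | 0.61 | 0.9 |
| 0.75 | 30% | 0.160 | 358 | 0.62 | 0.67 | 1.2 |
| 0.75 | 50% | 0.185 | 304 | 0.66 | 0.70 | 1.4 |
| 0.80 | 20% | 0.183 | 309 | 0.65 | 0.70 | 1.4 |
| 0.80 | 30% | 0.228 | 240 | 0.71 | 0.75 | 1.8 |
| 0.80 | 50% | 0.261 | 205 | 0.74 | 0.78 | 2.1 |

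The most favourable row still needs 205/76 = 2.7 times the planned enrolment.

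**4. Continuous primary endpoint.** S = 1 + (p − 2) / [n ln(1 − R²app)], with R²app = [R²(n − p − 1) + p] / (n − 1). For p = 7, n = 61 and R² = 0.36: R²app = (0.36 × 53 + 7)/60 = 0.435, ln(0.565) = −0.570, and S = 1 − 5/(61 × 0.570) = 0.856.

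| Assumed R² | S at 61 | S at 76 | n for S ≥ 0.90 |
|---|---|---|---|
| 0.20 | 0.764 | 0.795 | 192 |
| 0.30 | 0.829 | 0.855 | 120 |
| 0.36 | 0.856 | 0.879 | 96 |
| 0.50 | 0.900 | 0.917 | 62 |
| 0.60 | 0.921 | 0.935 | 47 |

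At n = 61 and R² = 0.36, 6 parameters give S = 0.88, 5 give 0.91 and 4 give 0.94. Five is therefore the most that meets 0.90.

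**5. The precision formula.** The large-sample variance of r is proportional to (1 − r²)², not (1 − r²).

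- With the square: 1.96² × 0.64² / 0.04 = 39.3, so 40 completers. Dividing the variance by n − 1 instead of n gives 41, and a Fisher-z interval gives 43.
- At 61 completers the half-width is 1.96 × 0.64/√61 = 0.16, and the Fisher-z 95% interval is 0.41 to 0.74.

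The missing square makes the sample larger than the stated precision requires.

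**The case against.** The strongest reply is that the section only names a target and an aim, and that the protocol plans elastic net, bootstrap optimism correction, and simplification or stronger penalisation if optimism is substantial. This stands in part. A reader might infer that the published accuracy will be over-optimistic. The documents do not support that, because they commit to optimism-corrected performance with calibration intercept and slope. But penalisation does not make 76 participants meet 0.90 with 7 parameters, and the target is offered as support for 76 with no calculation behind it.

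A second reply is that R² = 0.36 is not the plan's figure. This is right. "r (Estimated Correlation value) = 0.6" is the input to a single-correlation formula, and several predictors together may explain more. A reader might infer that the primary model fails the target on the protocol's own numbers. It does so only if the square of that r is taken as the multivariable R²; at about 0.50 the gap closes.

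Third, the large shortfalls concern dichotomised outcomes, which are secondary, and they rest on an assumed prevalence. That is true, though the conclusion holds at every prevalence tried.

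Fourth, because "Independent variables (predictors) will be measured at two points", a reader might count 18 candidates (nine muscles, twice). The Abstract and Background limit the aim to sEMG from the first week, so 18 is not supported. With separate limb models, the five upper-limb or four lower-limb muscles alone already meet 0.90 at R² = 0.36.

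Finally, a reader might blame the missing square or the rounding for the shortfall. Neither causes it: the first errs on the safe side, and the second costs one or two participants.

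**Conclusion.** The point holds in this form: the stated combination of 76 participants, 10 events per parameter, about 7 parameters, shrinkage of at least 0.90 and AUC 0.75–0.80 is not attainable.

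- **Events rule:** it supports 3 parameters at best for a binary outcome and does not apply to the primary endpoint. This needs no assumption.
- **Secondary binary models:** with 7 parameters, about 205–358 participants are needed at prevalence 30–50%. Sixty-one completers give about 0.62–0.74 and support 1–2 parameters. This rests on the assumed prevalence and a normally distributed linear predictor in each class.
- **Continuous primary endpoint:** the shortfall is modest, 0.86 (n = 61) to 0.88 (n = 76) against 0.90 if R² = 0.36. It closes at 61 if R² is about 0.50. The protocol states no R², so neither case can be claimed as planned.

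The documents do not show that the study is too small for its primary purpose. They show that its justification is wrong as written. The precision formula and the rounding are minor corrections.

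**What to change.** Keep 76 and rewrite the Sample size estimation section:

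- Delete the events-per-predictor justification for the continuous endpoint.
- State the assumed multivariable R² and the shrinkage expected at 61 completers.
- Limit the candidate week-1 parameters, counted before elastic-net selection, to what meets 0.90. At R² = 0.36 this is 5 per limb model (S = 0.91). The muscles of one limb alone fit. In the upper-limb model any added covariate requires summarising muscles; the lower-limb model has room for one more parameter. Align the wording on prespecification with the elastic-net sentence accordingly.
- State that the dichotomised models assessed by AUC do not meet 0.90 and are exploratory.
- Correct the precision formula to (1 − r²)² and report what 61 completers give: a half-width of about 0.16 (95% CI 0.41–0.74 around r = 0.6).

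The cost is rewording, a less favourable stated figure and fewer candidate predictors. No extra participants are needed. It is best done before any model is fitted.

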## Procedure

All patients admitted with acute stroke to the study center during the recruitment period will be consecutively screened within the first week of stroke onset for eligibility. A screening log will be maintained to document the number of patients screened, included, excluded (with reasons), and those who decline participation. Information recorded in the screening log will inform the final participant numbers, as summarised in the study flow diagram (Fig. 1). Patients who fulfil the inclusion criteria will be requested to participate in the study. The measurements will be recorded the next day after the consent for participation. Raw sEMG signals will be collected from the paretic side at two time points—within 7 days and again at 30 days after stroke onset and processed via Lab Chart 8.1.30 software. The raw data (%Maximal Voluntary Contraction) will be normalized by the mean Root Mean Square (RMS) /max RMS X100, which will be used for analysis. Mean RMS will be computed for each 10-second trial during task execution and then averaged across trials. The following clinical assessments will be collected at the 1st and 3rd months after stroke onset: Fugl Meyer Assessment (FMA), Action Research Arm Test (ARAT), Functional Ambulation Category (FAC), 10-meter Walk Test (10MWT), Mini BEST, and Stroke Impact Scale (SIS)Version 3.0. During the hospitalization phase, all the measurements will be performed in a quiet room next to the stroke unit. During follow-up, a recording will be performed at the physiotherapy department. To minimise detection bias, assessors conducting clinical outcome assessments at the 1st and 3rd month follow-ups will be blinded to baseline sEMG measurements. Assessments will be performed by a licensed neurophysiotherapist with formal training in standardised stroke outcome measures. The investigator responsible for sEMG acquisition will be a neurophysiotherapist trained in sEMG recording, will not be involved in outcome assessments, and will remain blinded to all follow-up outcomes.

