## Variable

### Independent variables (Predictor)

#### EMG recording

The upper and lower limb muscles of the affected side will be monitored via an 8-channel AD equipment from Delsys, a Trigno™ wireless EMG system (Delsys Inc., Natick, MA, USA; Model number: DSY-DS-T01D-4, 2016; Base Station ID: BID-1437; Sensor dimensions: 27 × 37 × 13 mm). The system will be operated with Lab Chart software (AD Instruments, Version 8.1.30) integrated with Trigno Control Utility (Version 3.6.0). Pre-amplifier gain and analogue bandwidth will follow the manufacturer's default settings.

To ensure correct fixation and avoid electrode and skin impedance, an alcohol-based scrub will be used to cleanse the skin. The recording area will be shaved, where necessary. The sensors will be secured to the skin with manufacturer-provided adhesives to ensure that the sensors will not fall off or move during recording. Sensors will be calibrated before each session by checking baseline noise and electrode impedance as per manufacturer guidelines. sEMG recordings at recruitment will be conducted in a quiet, separate room under standardised clinical conditions. Efforts will be made to minimise electrical interference and movement artefacts by positioning participants comfortably, avoiding proximity to high-power electrical equipment where possible, and ensuring stable wireless signal transmission.

Raw sEMG signals will be acquired at the 1000 Hz sampling frequency and preamplified (0–1.5 mv) using a Delsys electromyography system. Signals will be processed using fourth-order band-pass filtered (20–500 Hz) to reduce motion artefacts and high-frequency noise, followed by full-wave rectification and sampling at 4 kHz and then processed with root mean square (RMS) using 20-ms epochs, corresponding to the instructed movement, excluding transition periods. Crosstalk will be quantified by computing inter-channel correlation during isolated contractions, and artefact rejection will be reported as the proportion of epochs excluded due to excessive noise or signal dropout.

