### Electrode placement & task instructions

Surface EMG sensors will be positioned over the muscle belly of the affected upper and lower limb muscles in accordance with SENIAM guidelines and aligned parallel to muscle fiber orientation [29]. For sEMG recording of each muscle, participants will be instructed to perform the corresponding functional movement (eg: elbow flexion movement for the sEMG recording of the biceps brachii muscle) as depicted in Figs. 2& 3. Assistance or gentle resistance will be provided by the therapist as appropriate, depending on the participant's level of paresis. Each contraction will be recorded for a duration of 10 s, and a total of three trials will be obtained. Detailed procedures for electrode placement and recording are provided in Supplementary File 1.

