## Quality control

### sEMG signal acquisition

Contraction tasks are standardised across participants. Visual inspection will be performed to identify artefacts related to movement, signal dropout, or excessive noise. Trials with a signal-to-noise ratio below 20 dB or excessive artefacts will be rejected. In such cases, recordings will be repeated where feasible; otherwise, affected trials will be excluded from analysis. Baseline noise levels will be checked before each recording session. Crosstalk will be minimised through SENIAM-based electrode placement, alignment with muscle fiber direction, and single-muscle task execution. All sEMG recordings will be conducted by a trained physiotherapist experienced in sEMG acquisition, following a predefined standard operating protocol, and supervised by an investigator team with over 20 years of experience in sEMG and neurorehabilitation research.

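### The analysed sEMG predictor is a mean-to-maximum ratio, apparently taken within the same paretic muscle, so it carries almost none of the amplitude that the hypothesis is about

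*Protocol article*

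**What the plan says.** In Background the hypothesis opens "We hypothesized that greater sEMG amplitude recorded within the first week post-stroke" and expects a positive association with recovery at 3 months. The section on sEMG analysis again describes the primary association as one with early amplitude.

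Procedure defines the quantity to be analysed. The raw signal, labelled as a percentage of maximal voluntary contraction, is to be "normalized by the mean Root Mean Square (RMS) /max RMS X100, which will be used for analysis". No other sEMG measure is named for the model. The numerator is the mean RMS of each 10-second trial, averaged over trials. EMG recording specifies "root mean square (RMS) using 20-ms epochs", and the task section gives three trials per muscle.

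Both places that name the side agree: "Raw sEMG signals will be collected from the paretic side at two time points" (Procedure) and "The upper and lower limb muscles of the affected side will be monitored" (EMG recording). The article describes neither a non-paretic reference nor a separate maximal contraction. It does not say which recording supplies max RMS, and it refers to Supplementary File 1 for placement and recording details.

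Three other rules bear on the point. Trials below 20 dB signal-to-noise are repeated where possible and otherwise excluded (sEMG signal acquisition). Missing predictors are imputed by chained equations, assuming data missing at random (Missing data). Sensitivity analyses on signal processing are supplementary and leave the main analysis as it stands (sEMG analysis).

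**The concern.** Expressing EMG as a percentage of a person's own maximum is meant to remove differences in scale between people. Here the difference in scale between patients is the hypothesised predictor: a muscle with more residual voluntary drive should give a larger signal. If the divisor comes from the same weak muscle, it shrinks with the numerator and the difference is lost.

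Every sEMG predictor offered to the elastic net would inherit this. The model might still predict, because steadiness or effort could relate to recovery, but the finding would not concern amplitude. A null finding would say equally little about it.

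**Working it through.** **Plan's own figure.** The article gives no figure for this index, so there is nothing to reproduce. The sample size of 76 plays no part in the argument.

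**Step 1, algebra.** Multiply a muscle's whole recording by any gain c > 0:

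mean(c·RMS) / max(c·RMS) = c·mean(RMS) / (c·max(RMS)) = mean(RMS) / max(RMS).

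If the maximum comes from a separate attempt by the same muscle, and the task is done at a fraction f of that effort, the ratio is f times a constant. The muscle's strength cancels again.

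**Step 2, simulation with noise.** From the article: three 10-s trials, 1000 Hz acquisition, 20-ms RMS epochs. Assumed, not in the article: Gaussian signal, additive noise with SD 1, a 20–450 Hz band (500 Hz is the Nyquist limit at 1000 Hz), the contraction shapes, and the window over which the maximum is taken. There were 100 replicates per scenario (50 in Step 4). The 20 dB limit corresponds to a signal of 10^(20/20) = 10 times noise.

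Steady contraction:

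| Signal ÷ noise | SNR (dB) | Mean RMS (noise units) | Ratio, max over 20 ms | Ratio, max over 0.5 s |
|---|---|---|---|---|
| 0 | none | 0.89 | 59.8% | 90.6% |
| 1 | 0 | 1.26 | 60.9% | 90.8% |
| 3 | 9.5 | 2.81 | 61.1% | 90.8% |
| 10 | 20 | 8.93 | 60.8% | 90.8% |
| 30 | 29.5 | 26.69 | 60.9% | 90.8% |
| 100 | 40 | 88.83 | 60.7% | 90.9% |

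From 1 to 100 times noise, mean RMS rises 88.83 / 1.26 = 70.5-fold and the ratio stays at 60.7–61.1%. Among trials that meet the 20 dB rule, mean RMS rises 88.83 / 8.93 = 9.9-fold and the ratio stays at 60.7–60.9%.

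**Step 3, other shapes, admissible trials only (10, 30 and 100 times noise, max over 20 ms).**

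| Shape | Ratio |
|---|---|
| Fluctuating | 53.9, 53.6, 53.3% |
| 3-s ramp | 53.1, 53.0, 52.4% |
| Decaying | 31.8, 30.3, 30.4% |
| 3-s burst | 25.5, 24.0, 23.7% |

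Within a shape, the ratio moves by at most 25.5 − 23.7 = 1.8 points over a tenfold range of signal. Between shapes, including steady, it runs from about 24% to 61%. Shape can therefore outweigh amplitude: a decaying contraction at 100 times noise has mean RMS 38.44 and scores 30.4%, while a steady one at 10 times noise has mean RMS 8.93 and scores 60.8%. That is 38.44 / 8.93 = 4.3 times the amplitude for half the score.

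**Step 4, a separate maximal attempt by the same paretic muscle (max over 0.5 s).** Full effort gives 90.7%, 91.0% and 91.0% at 10, 30 and 100 times noise. Half effort gives 45.4% and 45.3% at 30 and 100 times noise, where the task signal is 15 and 50 times noise and so passes the rule. The ratio follows effort, not strength.

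**The case against.** The best defence is that the article does not say where max RMS comes from. The percentage-of-maximum label fits a separate maximal trial, and Supplementary File 1 might describe one. This stands as a reason not to assert the source as fact. It does not rescue the predictor: with only the paretic side recorded, a separate maximum would apparently still be that muscle's own, and Step 4 covers that case.

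Some stronger readings are tempting, and the documents do not support them.

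- A reader might infer that pure noise scores highest. It roughly ties with a steady contraction (59.8% against about 61%), and noise-only trials fail the 20 dB rule.
- A reader might infer that the ratio falls as activity rises. That appears mainly below 20 dB and only for assumed uneven shapes; among admissible trials it is close to flat.
- A reader might infer that the hypothesis is untestable. Raw signals are acquired and mean RMS is computed, so amplitude can be recovered.
- A reader might set "Assistance or gentle resistance will be provided by the therapist as appropriate" against "Contraction tasks are standardised across participants" and see a contradiction. Movement, duration and number of trials can be fixed while support varies, and the matter has no bearing on scaling.

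The planned sensitivity analyses also count for something, as does the article's acknowledgement that normalisation adds uncertainty. But they are supplementary and leave the primary predictor unchanged.

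**Conclusion.** The point holds for the predictor as defined. Whether max RMS comes from the task trials or from a separate attempt by the same paretic muscle, the analysed percentage reflects contraction shape or relative effort and almost none of the between-patient amplitude named in the hypothesis. For a steady contraction, a 70-fold rise in mean RMS leaves it at about 61%; the 20 dB rule removes noise but does not restore amplitude. A null or a positive result could not be read as evidence about amplitude.

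The algebra needs no assumption beyond a same-muscle maximum, which is a strong inference from paretic-only recording rather than an explicit statement. The percentages depend on the assumed signal model and on the window for the maximum (about 61% at 20 ms, about 91% at 0.5 s), but the flatness does not.

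The 20 dB rule has a side effect. Muscles with little or no activity become excluded trials and may then be imputed as missing at random, although they are missing because their signal is low.

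**What to change.** Before the baseline sEMG data are analysed:

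1. State which recording supplies max RMS, and over what window.
2. Prespecify log mean RMS in microvolts as the primary sEMG predictor. Its ratio to a same-session resting RMS is an alternative if a resting segment is stored; the article mentions a baseline noise check before each session but not that a resting record is kept.
3. Keep the mean-to-maximum percentage as a sensitivity analysis.
4. State how a muscle with no signal above the 20 dB limit is scored, rather than leaving it to exclusion and imputation. Mean RMS stays positive in a silent muscle (0.89 noise units in the simulation), so its logarithm exists and such a muscle could be kept at the low end of the scale.

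The cost is a change of wording and some reprocessing of signals that are recorded anyway; acquisition need not change. The downside is that absolute RMS carries more electrode and skin variability. A resting reference would remove part of it, and the standardised placement and skin preparation already planned help to limit it.
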